### **Hypotheses:**

**Alternative Hypothesis:** Early multimodal therapy significantly reduces the number of days of invasive mechanical ventilation compared to late multimodal therapy in intubated patients in the intensive care unit.

**Null Hypothesis:** There are no statistically significant differences in the number of days of invasive mechanical ventilation when comparing early multimodal therapy to late multimodal therapy in intubated patients in the intensive care unit.

## **6. Methodology**

### *6.1. Study design*

A phase III, randomized, controlled clinical trial will be conducted at a single center, with two parallel groups of patients. Patients who meet the inclusion criteria will be assigned, through stratified randomization by sex and age group, to one of the two study groups at a 1:1 ratio. Allocation concealment will be achieved using opaque, sealed, and sequentially numbered envelopes. In the first group, called the "early arm" (EA), patients who have been intubated in the intensive care unit or the emergency and/or surgery rooms will be included, and they will receive multimodal therapy early (<24 hours). In the second group, called the "late arm," multimodal therapy will also be applied, but it will start at 72 hours of mechanical ventilation. Due to the methodological characteristics of the study, it will not be possible to blind the participants or the researchers regarding the group to which they belong. However, the healthcare professionals who will perform the final evaluation on day 90 of follow-up will not be informed about the intervention group the participant was in. Similarly, the statisticians and epidemiologists who will analyze the data will be blinded to the intervention performed in each group. Finally, the study will be analyzed by intention to treat.

## 6.2. Population

**Inclusion Criteria:** Must meet all the following criteria:

Adult patients (over 18 years old)

Patients hospitalized in the adult intensive care unit at Fundación Santa Fe de Bogotá who require invasive mechanical ventilation through an endotracheal tube for a period longer than 24 hours.

Barthel Index greater than or equal to 70

**Exclusion Criteria:**

Patients requiring invasive mechanical ventilation through a tracheostomy cannula or nasotracheal tube

Patients who have undergone any type of head and neck surgery

Cardiac arrest

Airway burns

Burns covering more than 50% of the body surface area

Patients with chronic obstructive pulmonary disease (COPD)

Patients referred from another institution

Demyelinating diseases or neuromuscular junction disorders

Patients requiring neuromuscular relaxation

Patients with a life expectancy of less than 180 days

Patients who, by medical criteria, would not benefit from multimodal treatment

Patients not admitted to the ICU for the first time

Patients participating in other rehabilitation clinical trials

Patients with liver or kidney transplants

Patients who have undergone cytoreductive surgery (Sugar-Baker)

### Evaluation and Patient Withdrawal Criteria:

**Changes in Participant's Health Status:** If a participant develops health conditions that could affect the validity of the results, such as acute myocardial infarctions, pulmonary thromboembolism, intracerebral hemorrhages, cardiac dysfunction (requiring inotropic support), and multiple surgical washouts.

**Lack of Compliance:** If a participant does not meet the study requirements or does not follow the protocol guidelines, they may be withdrawn to maintain data integrity.

**Participant Decisions:** A participant has the right to withdraw from the study at any time for any reason, without penalty.

**Interim Results:** If significant results are discovered during the study that make it ethically necessary to stop the study to protect participants.

**Study Completion Criteria:** Once sufficient data have been collected to answer the research questions, the remaining participants may be withdrawn.

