### 6.8 Losses and Handling of Missing data

- Frequency and Distribution: Losses during follow-up were recorded for participants in both study groups. Of [total number of participants] initially assigned, [number of participants lost] were lost during the study period.
- Reasons for Losses:
  - o Voluntary withdrawal of consent by the participant.
  - o Adverse events not related to the study treatment.
  - o Failure to comply with the study protocol.
  - o Transfer to other medical facilities.
- Comparison between Groups: A comparative analysis will be carried out between the control and intervention groups, to assess the equitable distribution of losses.
- Characteristics of Lost Participants: The baseline demographic and clinical characteristics of participants who completed the study will be compared with those who were lost to follow, to assess whether the losses introduced substantial biases.

- **Impact on Analysis:** A sensitivity analysis will be performed to evaluate the potential impact of losses on the study results. Results will be presented with both the inclusion and exclusion of missing participants.

- **Statistical Management:** In the main statistical analysis, the intention-to-treat approach will be used, including all participants according to their original assignment, regardless of their compliance or loss to follow-up. We will also perform a sensitivity analysis based on a per-protocol analysis since it could provide us with a measure of the effect of weaning under ideal treatment adherence conditions.

- **Replacement of Lost Participants:**

- o **Ethical Consideration:** Before considering the replacement of lost participants, an ethical evaluation of the justification for such action will be conducted. It will be considered whether the replacement is ethically acceptable and whether its implementation respects the rights and well-being of the participants.

- o **Imputation Methods:** If replacement of lost participants is considered, statistically sound and well-founded imputation methods will be used. Options such as imputation by the mean, LOCF, or other more advanced methods such as multiple imputation will be explored.

- o **Transparency and Documentation:** A detailed description of the imputation methods used will be provided, including the reasons for choosing a specific method. This will be included in the final reports and communication with the Ethics Committee.

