## 6.9. Protocol Adherence Criteria

Adherence to the protocol will be evaluated in several crucial aspects and will be categorized as high or low. Patients with low adherence to the protocol will be excluded from the sensitivity analysis by intention protocol but will be included in the analysis by intention to treat.

- **Patient withdrawal:** Low adherence will be considered when a patient voluntarily requests withdrawal of consent, experiences an adverse event unrelated to the study treatment, or is transferred to other medical facilities.

- **Non-compliance with the study protocol:** It will be classified as low adherence when a patient cannot receive 80% of the interventions required according to the protocol.

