A detailed exploration will be conducted through a sensitivity analysis of possible interactions between identified subgroups, according to the RASS scale, protocol adherence, and other relevant variables, to deepen the understanding of any joint influence that may affect the study results. If no statistically significant differences are identified through regression analyses, a post-hoc analysis will be conducted to assess whether the recruited sample size was adequate to detect possible differences between the established subgroups. This additional analysis will allow adjusting the interpretation of the results and provide valuable information on the validity of the obtained conclusions.

Finally, an independent data monitoring committee will be established to conduct interim reviews of the sample size, allowing adjustments based on variations in event rates observed during the study, thus ensuring adequate statistical power throughout its execution.

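### Section 6.2 allows randomised patients to be withdrawn for complications, non-compliance or enough data, so outcomes that the intention-to-treat analysis needs may be lost

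*Protocol*

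**What the plan says.** Protocol section 6.2, under Evaluation and Patient Withdrawal Criteria, lists several grounds for withdrawal after randomisation. Three matter here:

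- Complications: "health conditions that could affect the validity of the results, such as acute myocardial infarctions, pulmonary thromboembolism, intracerebral hemorrhages", followed by cardiac dysfunction needing inotropes and repeated surgical washouts.
- Non-compliance: "If a participant does not meet the study requirements or does not follow the protocol guidelines, they may be withdrawn to maintain data integrity".
- Enough data: "Once sufficient data have been collected to answer the research questions, the remaining participants may be withdrawn".

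Section 6.1 states that the study is analysed by ITT. Section 6.8 describes that analysis as "including all participants according to their original assignment, regardless of their compliance or loss to follow-up". Section 6.9 keeps low-adherence patients in the ITT analysis and removes them only from the per-protocol sensitivity analysis.

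Section 6.8 also lists failure to comply among the reasons for loss. It then discusses replacing lost participants: "Options such as imputation by the mean, LOCF, or other more advanced methods such as multiple imputation will be explored".

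Section 6.1 says that neither participants nor researchers can be blinded. Section 6.13 analyses time on ventilation with extubation yes/no, by univariable Cox regression and a log-rank test.

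**The concern.** An ITT analysis needs two things: a set containing everyone randomised, and an outcome for each of them. The protocol secures the first. Section 6.2 puts the second at risk, because a patient withdrawn from the study on day 2 may have no recorded extubation time.

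The listed complications occur after allocation and plausibly go with longer ventilation, although the documents do not state that link. The non-compliance ground has no threshold and is optional. The people applying both know the arm. If they withdraw patients more readily in one arm, the patients with usable outcomes are no longer comparable between arms. With 37 per arm, a few such removals count, and no later analysis plan can recover ventilation times that were never recorded.

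**Working it through.** **Text comparison.** The claim rests on no figure in the protocol, so the first step is to look for any sentence that keeps withdrawn patients under observation.

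- Section 6.2 calls its list withdrawal criteria and says nothing about later data collection.
- Discontinuation of therapy (section 6.7) says that clinical care continues after the intervention is interrupted. It does not mention outcomes. Its own list mixes stopping therapy with a physician ending study participation and with withdrawn consent.
- Section 6.8 includes lost patients in ITT, but it treats non-compliers as lost and turns to replacement or imputation.
- Section 6.11 plans a day-90 telephone contact for mortality, with no statement about withdrawn patients.
- Inotropic support is a withdrawal ground in 6.2. It is also a study variable in 6.11, and Annex 1 (physiotherapy) sets a session length for patients receiving it. These passages must be reconciled.

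No passage separates stopping therapy from leaving follow-up.

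**Illustration of size.** Assumptions, none from the protocol except 37 per arm:

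- lognormal ventilation time, median 5 days, log-SD 0.6;
- 15% or 30% of patients have a complication that doubles ventilation time;
- true hazard ratio (HR) for extubation, early versus late, of 1;
- univariable Cox model, two-sided test at 1.96, 3,000–4,000 runs per scenario (simulation noise on a 5% error: 1.96 × √(0.05 × 0.95 / 4,000) ≈ 0.7 percentage points).

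Withdrawn patients are either excluded or censored at a time between day 1 and day 3. An HR above 1 favours early therapy.

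| Complicated patients | Withdrawn, early / late | Excluded: HR, type I error | Censored day 1–3: HR, type I error |
|---|---|---|---|
| 15% | 50% / 50% | 1.00, 5.6% | 1.00, 5.5% |
| 15% | 80% / 20% | 1.13, 7.7% | 1.11, 6.8% |
| 15% | 20% / 80% | 0.89, 7.2% | 0.90, 7.3% |
| 30% | 50% / 50% | 0.99–1.00, 5.5–5.7% | 1.01, 5.1% |
| 30% | 80% / 20% | 1.24, 12.7–13.1% | 1.22, 11.4% |
| 30% | 20% / 80% | 0.80–0.81, 12.8–13.6% | 0.81, 12.9% |

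With no withdrawal, the HR is 0.99–1.00 and the error 4.5–5.9%. Censoring at a random point of each patient's own ventilation time also gave almost no bias (HR 0.99–1.00, error 5.3–6.5%).

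In patient numbers, the 15% scenario means 37 × 0.15 × 0.8 = 4.4 withdrawn in one arm and 37 × 0.15 × 0.2 = 1.1 in the other. Both are within the 6 per arm that section 6.3 adds for losses. The 30% scenario means 8.9 and 2.2, so one arm exceeds that allowance.

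**The case against.** The strongest reply is that the protocol already protects ITT. Sections 6.8 and 6.9 keep non-compliant and lost patients in the set, and section 6.8 compares losses between arms and reports results with and without missing participants. This stands as far as the analysis set goes. It does not supply outcomes that were never collected; it only shows afterwards how many are missing.

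It is also true that bias is not automatic. Equal withdrawal produced almost none, the result depends on how and when withdrawn patients are censored, and no passage says that withdrawal will differ by arm.

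A reader might infer four stronger points that the documents do not support:

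- *Harms disappear from the data.* Section 6.7 plans continuous safety measurement, and nothing says that recorded events are deleted.
- *Repeated efficacy testing inflates type I error.* The interim clause, "If significant results are discovered during the study that make it ethically necessary to stop the study to protect participants", concerns protection of participants. Section 6.13 gives the committee the task "to conduct interim reviews of the sample size, allowing adjustments based on variations in event rates observed during the study". Neither states an efficacy look at 0.05, and stopping boundaries may properly be left to an analysis plan or committee charter.
- *The per-protocol analysis is heavily selected against fast late-arm patients.* The rule is: "It will be classified as low adherence when a patient cannot receive 80% of the interventions required according to the protocol". If nothing is required before the late arm starts, a patient extubated earlier has missed nothing. Therapy also continues until ICU discharge (6.5), and Annex 1 lists sessions for patients already off the ventilator. A large shift also needs a wide assumed spread. With the control figure in section 6.3, 6.1 ± 1.4 days, only 0.1% (lognormal) to 1.3% (normal) of patients fall below 3 days, and excluding them moves the mean by less than 0.05 day. What remains is an ambiguity about which sessions are required.
- *Mean or last-observation imputation is the chosen method.* The text is conditional and also names multiple imputation. The fair point is only that these two do not suit a time to extubation and should not be on the list.

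**Conclusion.** The point holds as a conflict between the withdrawal rules in section 6.2 and the ITT analysis promised in 6.1, 6.8 and 6.9. The analysis set is right; the outcome data it needs may be lost under discretionary criteria applied by unblinded staff. This can bias the primary comparison, in a direction that cannot be known in advance.

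The size is illustrative. If four in five complicated patients are withdrawn in one arm and one in five in the other, a null HR moves to roughly 1.11–1.24 or 0.90–0.80, with type I error of about 7–14%. This rests on the assumed duration distribution, complication frequency and doubling of ventilation time, and on withdrawal that differs by arm. If withdrawal is equal, the main consequence is lost information rather than bias.

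The enough-data clause is a separate weakness in the same list. It has no number, date or rule, and it can cut short the follow-up of patients still in the trial.

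**What to change.** - State that stopping study therapy is not withdrawal from the study. When therapy stops is a clinical decision; the investigators must reconcile sections 6.2 and 6.7 on it.
- Limit withdrawal from follow-up to withdrawn consent. For every other randomised patient, collect ventilation time, day-28 and day-90 outcomes and safety events, and analyse by ITT.
- Delete withdrawal for non-compliance and the enough-data clause. The trial then ends with the planned 74 patients and completed follow-up, unless the monitoring committee changes this.
- Do not replace randomised patients. Do not use mean or last-observation imputation for time to extubation; censor at last contact.
- In the per-protocol sensitivity analysis, state that no session counts as required of a late-arm patient before that arm's start, which is 72 h in sections 6.1 and 6.5, so that early extubation is not scored as low adherence. Annex 1 describes the late start differently for several therapies, and this must be reconciled. Do not exclude patients because of adverse events.

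The cost is a wording amendment and continued data collection on patients whose therapy has stopped, many of whom are likely to be still in the ICU.

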| Time | 
Screening: Verification of the inclusion and exclusion criteria of patients will take a maximum of 24 hours after endotracheal intubation.
 
Intervention: For both study groups, multimodal therapy will be applied exclusively while the patient is in the ICU.
 
Follow-up:
 
At the beginning of the study, the variables described in point 6.6 will be measured.
 
At the time of weaning from ventilatory support, the following variables will be measured: delta POCC, muscle pressure, P0.1, number of secretions per orotracheal tube, asynchrony index, NIF, % leak, peak cough flow, measurement of diaphragmatic excursion,
                                                                                                                                                                        |

|  |                                                                                                                                                                                                                                                                                                             |
|--|-------------------------------------------------------------------------------------------------------------------------------------------------------------------------------------------------------------------------------------------------------------------------------------------------------------|
|  | 
measurement percentage of diaphragmatic thickness, and tracheobronchial secretions.
 
On the day of hospital discharge, the variables recorded in point 6.6 will be measured.
 
The last measurement of variables will be carried out 90 days after the patient is intubated by point 6.6.
 |
|--|-------------------------------------------------------------------------------------------------------------------------------------------------------------------------------------------------------------------------------------------------------------------------------------------------------------|

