### 6.3. Sample size

Based on the study published by Schweickert et al. where they found that the mean number of days of mechanical ventilation in patients with usual physical therapy was  $6.1 \pm 1.4$  days and in early therapy it was  $3.4 \pm 1.25$  days (32), for an alpha error of 0.05 and a statistical power of 0.8 is considered the following formula:

$$ES = \frac{|\mu_1 - \mu_2|}{\sqrt{DE1^2 - DE2^2/2}}$$

$$ES = \frac{|6.1 - 3.4|}{\sqrt{1.40^2 - 1.25^2/2}}$$

$$ES = \frac{2.7}{\sqrt{3.52/2}}$$

$$ES = 2.03$$

With the effect size calculated ( $ES \approx 0.4463$ ), we can use the formula for the sample size mentioned earlier:

$$n = \frac{2 \left( \frac{Z\alpha}{2} + Z\beta \right)^2 \cdot (\sigma_1^2 + \sigma_2^2)}{ES^2}$$

Where  $\frac{Z\alpha}{2}$  is the critical value corresponding to the alpha significance level /2 to  $\alpha = 0.025$ ,  $\frac{Z\alpha}{2} \approx 2.81$

and  $Z\beta$  is the critical value corresponding to the statistical power beta to  $\beta = 0.90$ ,  $Z\beta \approx 1.28$

The other values we have are the same:

- Mean of group 1 ( $\mu_1$ ) = 6.1 days
- Standard deviation of group 1 ( $\sigma_1$ ) = 1.4 days
- Mean of group 2 ( $\mu_2$ ) = 3.4 days
- Standard deviation of group 2 ( $\sigma_2$ ) = 1.25 days

Effect size ( $ES$ )  $\approx 20.03$  (previously calculated)

Substituting these values into the formula:

$$n = \frac{2 (2.81 + 1.28)^2 \cdot ((1.40)^2 + (1.25)^2)}{(2.03)^2}$$

$$n = \frac{2 (4.09)^2 \cdot (1.96 + 1.56)}{4.13}$$

$$n = \frac{2 (16.72) \cdot (3.52)}{4.13}$$

$$n = \frac{(35.35) \cdot (3.52)}{4.14}$$

$$n = 30.29$$

Rounding:

$$n = 31 \text{ by each group}$$

To the estimated 31 patients per arm, an extra 20% (6 patients per arm) is added to minimize the loss of statistical power in case patients withdraw from the study or there are missing data.

The sample size has also been determined based on the magnitude of the expected effect of mobilization within 48-72 hours of mechanical ventilation, as suggested in the reference study (33), which justifies our choice to evaluate early mobilization at 24 hours versus 72 hours after mechanical ventilation in our study.

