## 10. Activity Schedule

| Activities                                        | Month1 | Month2 | Month3 | Month4 | Month5 | Month6 | Month7 |
|---------------------------------------------------|--------|--------|--------|--------|--------|--------|--------|
| Project Approach                                  | x      |        |        |        |        |        |        |
| Submission
Subdirectorarte clinical
studies |        | x      |        |        |        |        |        |
| Ethics committee
approval                      |        | x      |        |        |        |        |        |
| Patient Registration                              |        |        | x      | x      | x      | x      |        |
| Statistical analysis and
results               |        |        |        |        |        | x      |        |
| Writing scientific article                        |        |        |        |        |        | x      | x      |

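### The protocol lets the trial end once data are judged sufficient, with no number or boundary, and its activity schedule puts the analysis in month 6, too early for the day-90 follow-up it requires

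*Protocol*

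**What the plan says.** **Ending the trial.** The last of the withdrawal criteria in section 6.2 reads: "Once sufficient data have been collected to answer the research questions, the remaining participants may be withdrawn". Nothing in the protocol says how much data is sufficient, who decides, when, or against what boundary. The sample is otherwise fixed: the Summary gives 74 patients, and section 6.4 repeats 37 per arm. Sections 6.1 and 6.8 commit to intention to treat, with everyone analysed as assigned whatever their compliance or loss to follow-up. Section 6.3 plans "for an alpha error of 0.05 and a statistical power of 0.8".

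**Neighbouring text.** The same list has a separate item on interim findings: "If significant results are discovered during the study that make it ethically necessary to stop the study to protect participants". Section 6.13 promises a multiplicity adjustment, offers several methods without choosing one, and does not link it to interim looks. It also says that "an independent data monitoring committee will be established to conduct interim reviews of the sample size, allowing adjustments based on variations in event rates".

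**Timing.** In the section 10 table the row "Patient Registration" is marked in months 3, 4, 5 and 6. Statistical analysis is marked in month 6 only, writing in months 6 and 7, and the table ends at month 7. The PICOT table in section 3 states: "The last measurement of variables will be carried out 90 days after the patient is intubated". Section 6.6 lists all-cause mortality to day 90 and several outcomes counted to day 28. Section 6.11 plans a telephone contact for mortality at day 90, and section 6.1 promises a final assessment then by staff unaware of the assigned arm. The Summary gives one year as the duration of both participation and study.

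**The concern.** The completion sentence makes the end of the trial depend on accumulating data, in a study where participants and researchers know the assigned arm. If sufficiency is judged by whether the arms already differ, the trial tends to stop on a favourable fluctuation. The false-positive rate then rises and the estimated effect is exaggerated. The sentence also removes patients who are enrolled but not yet followed up, so their later outcomes go uncollected because of a study decision rather than anything that happened to them. That is hard to square with analysing all participants as randomised.

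The timetable raises a different problem. Analysis in the last registration month cannot include complete 90-day mortality or the complete day-90 assessment. It also leaves some patients short of day 28, the horizon of the listed secondary outcomes on ventilator-free, delirium and sedation days.

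**Working it through.** **1. Planned size.** Section 6.3 adds 6 to 31 per arm: 31 + 6 = 37, and 2 × 37 = 74, as the Summary states. This is the only quantity of data that the protocol fixes. The completion sentence does not refer to it.

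**2. What repeated looks would cost, if that is how the sentence were used.** The input from the protocol is the nominal level 0.05 (section 6.3). Two-sided testing, the number of looks K and equal spacing are assumptions. With no true effect, let Z_j be the test statistic at information fraction j/K. The error rate is the probability that the largest of |Z_1|, …, |Z_K| exceeds 1.96. Simulation of 400,000 sequences gives:

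| Looks K | Type I error |
|---|---|
| 1 (check) | 0.050 |
| 2 | 0.083 |
| 3 | 0.107 |
| 5 | 0.14 |
| 10 | 0.19 |

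The protocol states no value of K, so no row of this table is a property of the plan.

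**3. Follow-up available in month 6.** From section 10, registration fills months 3 to 6. Assume 30-day months and even accrual, so 74 patients enter over 120 days. At t days after registration opens, the share of the 74 who have passed f days of follow-up is (t − f)/120, limited to between 0 and 1.

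| Time | t | Past day 90 | Past day 28 |
|---|---|---|---|
| Start of month 6 | 90 | 0/120 = 0% (0) | 62/120 = 52% (about 38) |
| Middle of month 6 | 105 | 15/120 = 12.5% (about 9) | 77/120 = 64% (about 47) |
| End of month 6 | 120 | 30/120 = 25% (about 18) | 92/120 = 77% (about 57) |
| End of month 7 (last column) | 150 | 60/120 = 50% (37) | 100% (74) |

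With 30-day months, only patients enrolled in month 3 can reach day 90 by the end of month 6, whatever the accrual pattern. The share passes one half only if more than half of all patients enter in that first month.

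**4. Earliest complete follow-up.** A patient enrolled on the last day of month 6 reaches day 90 at t = 120 + 90 = 210 days. That is seven months after registration opens, the end of month 9. The 7-month table stops two months short of this. The one-year duration in the Summary would hold it but does not match the table.

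**The case against.** The completion sentence names no test, p-value or comparison of arms. Since the sample is fixed elsewhere, it can be read as meaning only that the study closes when the planned patients are in. That reading is possible, but the sentence does not say it, and it provides for withdrawing participants who remain, which closing at the planned size would not need. A separate statistical analysis plan could add a boundary, but this open permission would still stand in the protocol beside it.

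A reader might infer more than the protocol supports:

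- *That the protocol plans repeated efficacy tests at 0.05.* It does not state any. The error rates above are conditional.
- *That the interim-findings item is a second efficacy stop.* It is limited to stopping where ethically necessary to protect participants. It is a protection clause and forms no part of this point.
- *That there is no type I error control at all.* Section 6.13 does promise a multiplicity adjustment. It is generic and not tied to interim looks.
- *That the sample-size review is unblinded.* It is given to an independent committee and based on event rates. Whether those are pooled over arms can properly be left to an analysis plan or charter.
- *That results are seen before enrolment ends.* A monthly grid with both activities in month 6 does not show their order within the month.

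On timing, it is fair to say that the primary outcome runs from intubation to extubation, with planning means of 3.4 and 6.1 days, so most of it is known early. Mortality to day 90 is exploratory in section 6.6, though the PICOT table in section 3 lists it as secondary. The one-year figure suggests that the table is a planning slip. This limits the consequence but does not remove the contradiction.

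**Conclusion.** The point holds in two parts.

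First, section 6.2 permits a data-dependent end, and withdrawal of patients still in follow-up, with no number, look time or boundary. This conflicts with the fixed 74 patients and the intention-to-treat commitment. If applied as unadjusted tests at 0.05, it would raise type I error to about 8% with two looks and 14% with five, on an assumed number of equally spaced looks.

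Second, the section 10 schedule cannot deliver the day-90 follow-up in sections 3, 6.6 and 6.11. During month 6, 0 to 25% of patients reach day 90 (at most about 18 of 74) and about 52 to 77% reach day 28, assuming even accrual and 30-day months. The 7-month table also disagrees with the one-year duration in the Summary. Time to extubation is less affected than the day-28 and day-90 outcomes.

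**What to change.** 1. In section 6.2, delete the study-completion sentence. Alternatively, replace it with a statement that the study is complete when the planned 74 patients have been enrolled and followed up, and that the final analysis is done only then.
2. In section 10, move statistical analysis to after the last patient's day 90. If registration runs to the end of month 6, that is after the end of month 9. Extend the table to match.
3. Reconcile section 10 with the duration in the Summary and with the day-90 follow-up in sections 3 and 6.11. Give patient participation and study duration as separate figures.

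The cost is protocol wording and an analysis about three months later (end of month 6 to end of month 9). The sample size does not change.
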